### Data and safety monitoring bodies

Both the SATURN trial and SATURN-MRI study are governed by the University of Cincinnati (UC) Institutional Review Board (IRB) which serves as the central IRB for sites in the United States. Individual Ethics Boards oversee the trial at participating Canadian and Spanish sites. The independent Data and Safety Monitoring Board (DSMB) is appointed by the US National Institute of Neurological Disorders and Stroke (NINDS) and is responsible for the oversight of the participants’ safety and advising NINDS regarding continuation/discontinuation of the trial. An independent Medical Safety Monitor is responsible for monitoring the study with regard to safety on an ongoing basis and communicating with the DSMB. The Data Coordination Unit at the Medical University of South Carolina (MUSC) is in charge of monitoring of the sites.

### Statistical considerations

#### Sample size calculations

The target sample size is 894, based on the following observations/assumptions. We previously reported that 57% of statin-treated patients admitted with acute lobar ICH had CMBs on MRI [6]. Although the estimated incidence rate of new CMBs per year in patients with lobar ICH on/off statins is unknown, the annual incidence rate in mixed stroke cohorts varies from 3 to 7% per year (average ~ 5% per year) [18–21]. In a cohort of 118 patients with probable CAA, 8.5% showed new CMBs without cSS progression, 18.6% showed cSS progression without new CMBs, and 9.3% showed new CMBs and cSS progression, for a total of 36.4% with progression of either CMBs and/or cSS over the 2.2 years of follow-up, or approximately 19% per year [18]. These data likely overestimate the incidence rate expected in SATURN-MRI because approximately 33% of SATURN patients are expected to have probable CAA, and another 40% possible CAA. Therefore, we opted to select a more conservative new CMB and/or cSS rate of 6% per year, for a total of 12% over 24 months in patients discontinuing statins. We postulated that statin therapy will increase the risk of new CMB and/or cSS at a rate that is similar to that reported for ICH in the SPARCL trial (HR 1.68, or absolute increase of 8% over 24 months). Based on these assumptions, a two-group comparison of independent proportions with 652 subjects will yield 80% power to detect an absolute increase of 8 percentage points associated with the continuation of statin therapy in SATURN. This sample size was further inflated to account for loss-to-follow-up (LTFU), withdrawal-of-consent, and death during the 2-year follow-up period of approximately 15%, as observed in other MRI sub-studies, such as NAVIGATE-ESUS [22] and PURE [23].

The sample size calculation assumes 1:1 statin continuation:discontinuation among subjects enrolled in the ancillary SATURN-MRI study, but this balance is not guaranteed. However, the power is maintained above 75% for allocation ratios in the interval between 0.6 (discontinuation arm 62.5% of the total sample) and 2.5 (discontinuation arm 28.6% of the total sample).

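### The 12% control-arm risk does not follow from the CAA mix and rates quoted beside it, and for a fixed 8-point increase it is not a conservative choice

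*Protocol article*

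**What the plan says.** All of this is in the Protocol article, Statistical considerations, Sample size calculations.

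- New CMBs occur at 3 to 7% per year (average about 5%) in mixed stroke cohorts. The rate in lobar ICH on or off statins is said to be unknown.
- A cohort of 118 patients with probable CAA had a "total of 36.4% with progression of either CMBs and/or cSS over the 2.2 years of follow-up, or approximately 19% per year".
- That figure is called a likely overestimate for this study because "approximately 33% of SATURN patients are expected to have probable CAA, and another 40% possible CAA".
- The planning value for patients discontinuing statins is then chosen: "Therefore, we opted to select a more conservative new CMB and/or cSS rate of 6% per year, for a total of 12% over 24 months".
- The effect is borrowed from a statin trial's ICH result: "HR 1.68, or absolute increase of 8% over 24 months".
- Power is stated on the absolute scale: "652 subjects will yield 80% power to detect an absolute increase of 8 percentage points".

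No rate is given for possible-CAA or non-CAA patients, and no weighted calculation leads to 12%.

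**The concern.** There are two separate problems.

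First, the CAA mix is the reason given for going below the CAA cohort's rate, but applying that mix does not bring the rate down to 6% per year. The probable-CAA third nearly uses up the 12% by itself.

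Second, power is stated for an absolute difference of 8 points. In this range the binomial variance rises with the control risk, so a low control risk makes power for a fixed difference look better. It is conservative only if a relative effect is held fixed.

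This paragraph is the justification for the size of the primary comparison. A null result would be read as having had 80% power against an 8-point harm, and the population described in the same paragraph does not assure that.

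**Working it through.** **Inputs from the document.** Control risk 12%, statin arm 20%, 652 subjects, 1:1 allocation, HR 1.68; 36.4% over 2.2 years in probable CAA; 33% probable CAA; 3, 5 and 7% per year in mixed stroke cohorts; target 894; loss about 15%. **Assumption.** Two-sided alpha of 0.05, since the section states neither alpha nor sidedness.

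**1. The plan's own figure.** With unpooled variance, n per arm = (0.12×0.88 + 0.20×0.80)×(1.960+0.842)²/0.08² = 326, or 652 in total, with 80.0% power. With pooled variance under the null, 326 per arm gives 79.7%. The stated figure reproduces. Powers below use the pooled form.

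**2. What probable CAA contributes over 24 months.**
- Linear scaling: 36.4%×2/2.2 = 33.1%; 0.33×33.1% = 10.9 points.
- Constant hazard: 1−(1−0.364)^(2/2.2) = 33.7%; 0.33×33.7% = 11.1 points.
- The document's 19% per year, doubled as it doubles 6%: 38%; 0.33×38% = 12.5 points, already above 12%.

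**3. What is left for the other 67%.** (12−10.9)/0.67 = 1.6%, or (12−11.1)/0.67 = 1.3%, over 24 months; below zero on the third reading. The quoted mixed-stroke range is about 6 to 14% over 24 months and counts CMBs only, whereas the primary outcome also counts new cSS. In the CAA cohort, cSS progression without new CMBs made up 18.6 of the 36.4 points.

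**4. Control risk if the other 67% follow the mixed-stroke rates (assumption).** Risk = 0.33×0.337 + 0.67×[1−(1−r)²]. For r = 3, 5 and 7% per year this gives 15.1%, 17.7% and 20.2%. Linear scaling gives 14.9%, 17.6% and 20.3%.

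**5. Power under each reading of the effect.** For the hazard-ratio column, the statin-arm risk is 1−(1−p)^1.68. Evaluable numbers are 652 as stated, and 894×0.85 = 760.

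| Control risk | +8 points, 652 | +8 points, 760 | HR 1.68, 652 |
|---|---|---|---|
| 12% | 80% | 85% | 73% (19.3% in statin arm) |
| 15.1% | 74% | 80% | 82% |
| 17.7% | 70% | 76% | 88% |
| 20.2% | 67% | 73% | 91% |

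At 17.7%, the difference detectable with 80% power is 9.1 points with 652 and 8.4 points with 760.

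**6. The two effect statements.** At 12%, HR 1.68 gives +7.3 points; 8 points matches a risk ratio (12%×1.68 = 20.2%). The section treats HR 1.68 and 8 points as the same thing, yet power moves in opposite directions under them as control risk rises.

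**The case against.** The strongest reply is that the effect is anchored on a relative measure. The 8 points come from applying 1.68 to 12%, and the primary test is a logistic regression, which estimates an odds ratio. Raising the baseline while freezing 8 points cuts the effect off from its source. With HR 1.68 held, power with 652 is 82 to 91% over the whole 15 to 20% range, and a low control risk is then conservative, as the document says. This stands, and it limits the conclusion. It does not rescue the text as written, because the power sentence names an absolute increase and nothing says which scale is fixed.

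The reply also has force on the inputs. The 15 to 20% range is constructed: the document gives no rate for two thirds of the population. The CAA figure comes from one cohort of 118 whose statin use is not reported here; if it included statin users and the study hypothesis is right, its rate overstates the discontinuation arm. Finally, 652 is the less favourable evaluable number; with 760, the low end of the range still reaches 80%.

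A reader might go further and infer that the 80% was miscalculated, or that the true power is 70%. The documents support neither. The 80% follows from its inputs, and 70% depends on an assumed rate, a fixed 8 points and 652 evaluable subjects.

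**Conclusion.** The 12% is inconsistent with the mix and rates cited for it. This holds under all three ways of annualising the CAA cohort and needs no outside figure, only that the cohort's rate applies to the probable-CAA third. The size of the gap does need an assumption: about 15 to 20% instead of 12% if the remaining patients behave like the mixed stroke cohorts.

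For the fixed 8-point increase that the section states, the lower rate is not conservative. Power over that range is about 74 to 67% with 652 and 80 to 73% with 760. If HR 1.68 is the fixed effect, power with 652 is about 82 to 91%. The finding is therefore an unreconciled planning input and an undefined effect scale. It does not show that the study is too small.

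**What to change.** In Sample size calculations:

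1. Reconcile the 12% with the quoted CAA mix, giving the rates assumed for possible-CAA and non-CAA patients, or explain why the cohort's rate is not applied to the probable-CAA third.
2. State whether 8 points or HR 1.68 is the fixed effect.
3. Limit the word conservative to the relative-effect scale, or delete it.
4. Restate power and the difference detectable with 80% power over control risks of 12 to 20%, at 652 and about 760 evaluable.

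Do not replace 12% with a single value such as 18%, which would rest on an equally unsupported assumption. Enrolment, conduct and the primary analysis stay as they are. The cost is wording and a short table; the drawback is a less favourable stated power for an 8-point increase.

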#### Analysis related to the primary objective

We hypothesize that the proportion of patients with new CMBs and/or cSS on end-study MRI will be higher in the continuation arm. This hypothesis will be tested via a logistic regression model relating the presence of new lesions to treatment assignment.

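### The stated power floor of 75% does not hold at an allocation ratio of 2.5 for the planned logistic test with 652 evaluable subjects (about 69–71%); the lower limit and the power at 1:1 stand

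*Protocol article*

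**What the plan says.** Under Sample size calculations, the article takes a two-year event proportion of 12% in the discontinuation arm ("for a total of 12% over 24 months in patients discontinuing statins") and a rise of 8 percentage points with continuation. It concludes that "a two-group comparison of independent proportions with 652 subjects will yield 80% power". The target is then inflated for losses of about 15%: "The target sample size is 894".

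The next paragraph turns to imbalance. It notes that "The sample size calculation assumes 1:1 statin continuation:discontinuation among subjects enrolled in the ancillary SATURN-MRI study", concedes that this balance cannot be guaranteed, and offers one reassurance: "the power is maintained above 75% for allocation ratios in the interval between 0.6 (discontinuation arm 62.5% of the total sample) and 2.5". The upper end is glossed as "2.5 (discontinuation arm 28.6% of the total sample", which fixes the ratio as continuation over discontinuation.

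Under Analysis related to the primary objective, the test is named: "This hypothesis will be tested via a logistic regression model relating the presence of new lesions to treatment assignment". The Data analyses section adds adjustment for the randomization covariates. The article states neither alpha nor sidedness, and it does not say whether the Wald, score or likelihood-ratio form of the test will be used.

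**The concern.** A power statement should describe the test that will be run. With equal arms, the usual tests of two proportions have nearly the same power, so sizing a logistic analysis by a two-proportion formula does no harm. With unequal arms they separate. The unpooled risk-difference variance gives the small arm its own binomial variance. When the small arm is the low-risk one, as at a ratio of 2.5, that variance is comparatively small and the formula looks favourable. Logistic tests do not share this advantage.

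The range is the article's only protection against imbalance. Participation is optional and there is no separate randomization for the MRI study. If the upper limit is too generous, the article claims more robustness than the primary analysis has when the discontinuation arm is short of subjects.

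**Working it through.** **Inputs.** From Sample size calculations: p₁ = 0.12 (discontinuation), p₂ = 0.12 + 0.08 = 0.20 (continuation), N = 652 evaluable, ratio r = n₂/n₁. Check of direction: 1/(1 + 0.6) = 62.5% and 1/(1 + 2.5) = 28.6% in the discontinuation arm, as the article states. Assumed: two-sided alpha 0.05. This reproduces 652, whereas a one-sided 0.05 test would need only about 518 by the pooled formula.

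**Step 1: reproduce the article's figures.** Unpooled formula: power = Φ(0.08/SE − 1.96), with SE = √(0.12·0.88/n₁ + 0.20·0.80/n₂).

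- Sample size: (1.960 + 0.842)² × (0.1056 + 0.1600)/0.08² = 325.7, so 326 per arm and 652 in total. This matches.
- r = 1 (326/326): SE = 0.02854, Φ(0.843) = 80.0%.
- r = 0.6 (407.5/244.5): SE = 0.03022, Φ(0.687) = 75.4%.
- r = 2.5 (186.3/465.7): SE = 0.03017, Φ(0.691) = 75.5%.
- This formula equals 75% at r = 0.584 and r = 2.594.

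The range from 0.6 to 2.5 is therefore the unpooled range at N = 652. At 760 the same formula gives 81.7% at 2.5, so the limits were not set there.

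**Step 2: pooled formula at r = 2.5.** The pooled proportion is (186.3·0.12 + 465.7·0.20)/652 = 0.1771, and the null SE is √(0.1771·0.8229·(1/186.3 + 1/465.7)) = 0.03310. Power = Φ((0.08 − 1.96·0.03310)/0.03017) = Φ(0.501) = 69.2%. This formula crosses 75% at r = 1.82.

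**Step 3: exact power of the logistic test.** With treatment as the only term, the logistic Wald, score and likelihood-ratio statistics depend only on the two event counts. Power is the sum of the binomial probabilities of all pairs of counts at which the statistic exceeds its critical value. At N = 652:

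| Ratio | n (disc./cont.) | Wald | Score | Likelihood ratio |
|---|---|---|---|---|
| 0.6 | 408/244 | 77.9% | 78.3% | 77.6% |
| 1.0 | 326/326 | 79.9% | 80.0% | 80.3% |
| 1.8 | 233/419 | 75.1% | 75.6% | 76.9% |
| 1.9 | 225/427 | 74.3% | 74.8% | 76.1% |
| 2.0 | 217/435 | 73.7% | 73.9% | 75.2% |
| 2.1 | 210/442 | 72.9% | 73.3% | 74.5% |
| 2.5 | 186/466 | 69.3% | 69.5% | 71.4% |

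The shortfall at 2.5 runs from 75 − 71.4 = 3.6 to 75 − 69.3 = 5.7 points. By the same enumeration, the unpooled z-test itself has 74.4% power at 2.5, so even the test behind the formula falls slightly short.

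**Step 4: the other possible basis.** 894 × 0.85 = 759.9, about 760. At r = 2.5 (217/543) exact power is Wald 76.3%, score 76.5% and likelihood ratio 78.1%. All exceed 75%.

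**The case against.** The strongest reply is that nothing was miscalculated. The article names a comparison of two independent proportions as its sizing method. With unpooled variance, that method reproduces 652, 80% and both ends of the range, and sizing a logistic analysis this way is routine. This is right as far as it goes. A reader might infer an arithmetic slip or a wrong sample size, and the article supports neither. What remains is that the range belongs to a different test from the primary one, and the difference matters at its upper end.

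Second, a 2.5:1 split is very unlikely if parent allocation is near 1:1 and opting in does not depend on arm (both assumed here). The article attaches no monitoring or tolerance rule to the range. This stands, and it limits the weight of the point. A reader might also infer that a drift to 2:1 would seriously damage power. It would not: at 2.0 the logistic tests have 73.7–75.2%, at most 1.3 points under the floor.

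Third, with 894 enrolled and 15% lost, the claim holds at 2.5. This is also true, but the article attaches its 80% to 652, and the range reproduces at 652 and not at 760.

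Fourth, the planned model is adjusted, and the figures above are not. Prognostic covariates could change power somewhat. The article gives nothing from which to quantify this, so it cannot be used to support the stated floor.

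**Conclusion.** The point holds, and it is minor. At 652 evaluable, the floor of 75% fails at the upper limit of 2.5 under all three forms of the unadjusted logistic test, by about 4 to 6 points. The supportable upper limit is about 1.8 (Wald or score) or 2.0 (likelihood ratio). The lower limit of 0.6 holds at about 78%, and power at 1:1 is 80% as stated.

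A larger gap of about 8 points might be read from the large-sample formula for the Wald test of the log odds ratio, which gives 66.7% at 2.5. That approximation is too pessimistic here: the exact Wald power is 69.3%.

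The conclusion rests on 12% vs 20%, two-sided 0.05 (assumed), no covariate effect, and 652 as the evaluable number. The last assumption decides the matter, since with about 760 evaluable the stated range is correct. The sample size and the choice of primary analysis are not called into question.

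**What to change.** Change one sentence in Sample size calculations, in one of two ways.

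- **Keep 652 as the basis.** Name the form of the logistic test and restate the upper limit for it: about 1.8 for Wald or score, about 2.0 for likelihood ratio. Add that power at 2.5 is about 69–71%. The lower limit of 0.6 can stay.
- **Use about 760 evaluable (894 less 15%) as the basis.** Say so. The range from 0.6 to 2.5 can then stay, with unadjusted logistic power of 76–78% at 2.5.

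In either case, state alpha and sidedness beside the figure. The cost is one sentence and, under the first option, a slightly less favourable figure. The sample size and the analysis do not change.

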### Data analyses

The primary analysis will be conducted according to the intention-to-treat principle, meaning that all subjects are analyzed as a member of the treatment group to which they were randomly assigned in SATURN, even if the subject crosses over from one treatment arm to another. Secondary analyses will be conducted according to an on-assigned-treatment analysis. All models will be adjusted for the aforementioned randomization covariates as specified for SATURN (statin dose and indication, current use of or intent-to-use oral anticoagulants and/or antiplatelets post-ICH, and severity of enrolling ICH) [14].

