**Methods:**

A target of 894 SATURN participants will undergo a baseline MRI within 7 days of randomization and a repeat MRI at the end of the 24-month follow-up period. Any SATURN subject without contraindication to MRI has the option to participate in SATURN MRI. MRIs will be reviewed by blinded central raters to assess for the presence and burden of markers of CSVD and their progression. The primary outcome is new cerebral microbleeds and/or sulci with cortical superficial siderosis identified on T2*-weighted (GRE, SWI or SWAN) images between baseline and end-study MRI. Additional outcomes include the progression of white matter hyperintensity and incidence of covert infarcts.

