### Randomization

Patients will be randomized into the SATURN trial using the following stratification variables: clinical site, statin dose and indication (primary vs. secondary prevention), current use or intent-to-use oral anticoagulants and/or antiplatelets in the long-term post-ICH, and severity of ICH upon presentation as assessed by baseline ICH volume. There is no additional randomization procedure for the SATURN-MRI ancillary study.

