### Imaging analyses

Experienced readers, blinded to clinical details including treatment assignment, at the imaging core lab at the Seaman Family MRI Center at the University of Calgary will analyze the images. FDA compliant OsiriX software (Pixmeo SARL, Geneva, Switzerland) will be used to view the images. All incident lesions will be defined according to consensus guidelines for CMBs detection and STRIVE [15]. CMBs will be categorized by number (0, 1–2, 3–10, or > 10) and location (lobar, deep, or mixed deep/lobar), while cSS will be categorized as focal (involving ≤ 3 sulci) or disseminated (if involving ≥ 4 sulci). Covert infarcts will be defined as lesions in a vascular territory that are hyperintense on T2-weighted or FLAIR and hypointense on T1-weighted images, and if subcortical, they need to be at least 3 mm in size and have a round or ovoid shape to distinguish them from a perivascular space. Infarcts will furthermore be classified by size (> 15 or ≤ 15 mm axial diameter) and location (including cortical vs. subcortical and by lobe). Dilated perivascular spaces (Virchow-Robin) will be distinguished from infarcts on the basis of location, morphology, diameter (generally < 3 mm), and the absence of gliosis. Diffusion-weighted (DWI) hyperintense lesions will be defined as remote areas outside of the perihematomal border that are hyperintense on DWI with either corresponding hypointensity or isointensity on acute diffusion coefficient (ADC) sequences. White matter hyperintensities (WMH) will be divided into periventricular or deep and rated visually using the Fazekas scale. Semi-automated quantitative measurement of WMH volume will also be carried out using a Lesion Extraction Tool (University of Calgary; Calgary, AB, Canada).

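### The primary logistic model omits baseline CMB/cSS burden, which is graded centrally for every MRI participant: a modest loss of efficiency and robustness, not an invalid test

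*Protocol article*

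**What the plan says.** The primary analysis is given in two places. Analysis related to the primary objective: "This hypothesis will be tested via a logistic regression model relating the presence of new lesions to treatment assignment". Data analyses: "All models will be adjusted for the aforementioned randomization covariates as specified for SATURN", with the covariates listed as "statin dose and indication, current use of or intent-to-use oral anticoagulants and/or antiplatelets post-ICH, and severity of enrolling ICH". Lost-to-follow-up and missing data gives the same list, with treatment, as the covariates of the primary analysis. The adjustment set is therefore stated in the article, not left open for a later document.

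Baseline burden is measured by design. The abstract's Methods say "A target of 894 SATURN participants will undergo a baseline MRI within 7 days of randomization", and Imaging analyses says "CMBs will be categorized by number (0, 1–2, 3–10, or > 10) and location", with cSS graded as focal or disseminated. In the analysis plan, baseline CMB/cSS enters only the secondary proportional hazards model for recurrent ICH, as an interaction with treatment.

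On balance, the Randomization section says "Patients will be randomized into the SATURN trial using the following stratification variables: clinical site, statin dose and indication (primary vs. secondary prevention", followed by antithrombotic use or intent and baseline ICH volume. It adds "There is no additional randomization procedure for the SATURN-MRI ancillary study". On acquisition, the MRI protocol section accepts GRE, SWI or SWAN at 1.5 to 3.0 T and asks sites to hold sequence and field strength constant within a participant where they can.

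**The concern.** When the outcome is change since a baseline scan, the state of that scan is the natural first covariate. Omitting a prognostic baseline variable from a logistic model weakens the test of treatment. It also leaves the estimate exposed to any chance imbalance on that variable. Stratification in the parent trial does not protect against such an imbalance, because no CMB or cSS measure is a stratifier and the MRI participants are an opt-in subset.

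The article itself treats baseline phenotype as relevant to new lesions. Its sample size section lowers the assumed event rate because only about a third of participants are expected to have probable cerebral amyloid angiopathy (CAA). For the cognitive and functional models, Analyses related to the secondary aims adds a baseline indicator of cognitive decline or dementia to the randomisation covariates. The primary imaging outcome gets no such baseline term.

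At stake are a few points of power and some robustness of the primary estimate. If the adjustment were added only after results were known, it would be open to challenge as post hoc.

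**Working it through.** **1. The plan's own figure.** Inputs from Sample size calculations: 12% vs 20% over 24 months, 1:1, 80% power. Two-sided alpha 0.05 is assumed, since the article does not state it. With unpooled variance:

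n per arm = (1.96 + 0.8416)² × (0.12×0.88 + 0.20×0.80) / 0.08² = 7.849 × 0.2656 / 0.0064 = 325.7, so 326 per arm and **652** in total.

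The stated 652 is reproduced. It is an unadjusted two-proportion calculation and takes no credit for covariates.

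**2. What the article implies about predictor strength.** No odds ratio (OR) between baseline burden and new lesions is given. The indirect evidence compares two kinds of cohort:

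- Probable CAA, new CMBs and/or cSS progression: 36.4% over 2.2 years.
- Mixed stroke cohorts, new CMBs only: 3–7% per year, average about 5%, or 6.6–15.4% (average 11%) over 2.2 years.

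Crude OR at the average: (0.364/0.636) / (0.11/0.89) = 4.6; range 3.1 to 8.1. This mixes two endpoints. For new CMBs alone, the CAA cohort had 8.5% + 9.3% = 17.8%, which gives (0.178/0.822) / (0.11/0.89) = 1.75. The evidence therefore does not fix the strength, and a range is needed.

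**3. Power at N = 652 with and without adjustment.** Simulated logistic Wald tests, marginal risks held at 12% and 20%, 4,000 to 6,000 replicates per scenario. CMB prevalence of 57% is from the article; all ORs are assumed.

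| Covariates in the adjusted model | Assumed ORs | Unadjusted | Adjusted |
|---|---|---|---|
| CMB presence | 2 | 80.4% | 80.7% |
| CMB presence | 3 | 80.0% | 81.0% |
| CMB presence | 5 | 79.5% | 81.4% |
| CMB presence | 8 | 80.6% | 83.5% |
| CMB grade (per step), cSS, sequence | 1.3, 1.5, 1.3 | 79.3% | 80.2% |
| CMB grade (per step), cSS, sequence | 1.6, 2, 1.5 | 79.9% | 82.3% |
| CMB grade (per step), cSS, sequence | 2, 3, 2 | 80.0% | 84.6% |

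The graded rows assume 43/25/20/12% across the four CMB categories, cSS in 20% and an even split of two sequences. A more extreme set (2.5, 5, 2) gives 79.9% to 87.6%, but nothing in the article supports ORs of that size.

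**4. Cost of extra parameters.** A separate simulation at N = 652 with six added covariate parameters gave 80.3% unadjusted and 80.4% adjusted when the covariates were uninformative. Gains were about 0.4, 3 and 5 points under weak, moderate and strong assumed effects.

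**5. Chance imbalance in CMB presence.** SD of the between-arm difference in prevalence = √(0.57 × 0.43 × 4 / 652) = 0.0388; 95% limit = 1.96 × 0.0388 = 7.6 points. The shift in the unadjusted risk difference at that limit is 0.076 × (risk with CMBs − risk without), with overall risk set at 16%, the mean of 12% and 20%:

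| Assumed OR | Risk without CMBs | Risk with CMBs | Shift |
|---|---|---|---|
| 2 | 11.0% | 19.8% | 0.7 points |
| 3 | 8.5% | 21.7% | 1.0 points |
| 5 | 5.8% | 23.7% | 1.4 points |
| 8 | 4.0% | 25.0% | 1.6 points |

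The largest shift is 1.6/8 = 20% of the target effect.

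**The case against.** The strongest case is that the choice is standard and nothing is broken. Adjusting for the randomisation covariates is defensible and consistent with the parent trial. Randomisation keeps the test valid, and chance imbalance is already covered by its type I error. The planned 80% does not rely on covariates. If 894 are enrolled and 15% are lost, 894 × 0.85 = 760 remain, and unadjusted power is then about 85%. All of this stands, and it limits the size of the point.

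Three stronger readings are tempting and are not supported:

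- *Baseline burden is a documented strong predictor of new lesions.* The Introduction links CMBs and cSS to first and recurrent ICH, not to new lesions. The probable-CAA contrast falls from an OR of about 4.6 to about 1.75 once both sides count CMBs only. For sequence and field strength, the article gives no figure at all.
- *The subset is unstratified.* Participants were randomised with stratification on site, statin dose and indication, antithrombotics and ICH volume. Only CMB and cSS are left out.
- *The model contains no imaging information.* ICH severity is assessed by ICH volume, so it does contain some.

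A further objection is that many extra parameters, against about 652 × 0.16 = 104 expected events, could cost more than they gain. The six-parameter simulation shows no loss with uninformative covariates, so this does not stand. The imputation model may already take further clinically relevant baseline variables, but these are not named, and each imputed dataset is still analysed with the primary model as specified.

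**Conclusion.** The point holds as an improvement in efficiency and robustness. The primary model, as the article fixes it, leaves out a baseline measurement that is graded for every MRI participant, is a plausible predictor of the outcome and is not balanced by design. The specified analysis is valid and its planned power does not depend on the omission.

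The gain is from about 80% to about 80–85% power at 652 evaluable participants, near zero if the markers predict weakly. Protection against imbalance is worth about 0.7 to 1.6 points of the 8-point target at the 95% limit. These figures rest on assumed ORs, an assumed split of CMB grades, an assumed cSS prevalence and sequence mix, and two-sided alpha 0.05. The case for acting is that the gain costs almost nothing, not that the loss is large.

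**What to change.** In Data analyses, add to the covariates of the primary logistic model: baseline CMB category (0, 1–2, 3–10, >10), baseline cSS (none, focal, disseminated), baseline T2* sequence and baseline field strength. Name the same variables in the imputation model. Report a standardised risk difference alongside the odds ratio, so that the result can be read on the scale used for the sample size.

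Use the baseline acquisition only. A change of sequence or field strength between baseline and follow-up arises after randomisation in an open-label trial, so keep it out of the primary model and examine it in a sensitivity analysis. Because the Intervention section places the baseline scan within 7 days of randomisation, some scans may follow allocation; state that baseline burden is treated as a pre-treatment measurement.

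The cost is a sentence or two, fixed before unblinding, using central readings already planned and acquisition details of the baseline scan. The addition is up to 3 + 2 + 2 + 1 = 8 parameters (three sequence types, two field-strength groups), slightly more than the six simulated. The downside is that the odds ratio becomes conditional on more covariates, which the standardised risk difference addresses.
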